## Abstract

**Introduction:**

Efficient neuromuscular coordination, appropriate landing and lower limb strength is a key factor in volleyball performance. Non-ideal body composition and poor landing may lead to injury risk and poorly affect the performance. This study aims to investigate the effect of 8-weeks integrated neuromuscular training program on anthropometric characteristics, body composition, jump-landing biomechanics, and vertical jump height among adult male volleyball athletes.

**Methods:**

This non-randomized matched controlled study will utilize 28 male volleyball players aged between 18 and 25 years. Following baseline assessment, participants will be allocated to experimental group (INMT along with volleyball training) and control group (volleyball training along with a structured resistance training program) using non-randomized allocation procedure and a set of predefined criteria. The intervention will last 8 weeks, with three sessions per week. Primary outcome parameters such as body composition, anthropometric profiles, landing kinematics will be assessed using bioelectrical impedance analysis and landing error scoring system. The secondary outcome, vertical jump height, will be analyzed using vertec jump tester respectively. Group × time interaction test will be computed using ANCOVA, adjusted for baseline/linear mixed-effects model. Secondary outcome *p*-values will be adjusted for multiplicity, using the Holm-Bonferroni method.

**Discussion:**

To address the gap in the literature, this study will examine whether INMT improves anthropometric and body composition profiles, jump-landing mechanics, and vertical jump height in male volleyball athletes. By testing at 8 weeks, the study may provide data on the velocity of neuromuscular adaptations, validating whether significant changes occur within this specific periods. In addition, the findings may contribute to the specific profiling of male volleyball athletes by establishing how INMT affects both body composition and biomechanical metrics (jump height, Landing Mechanics) specifically in this population.

**Clinical Trial Registration:**

ClinicalTrials.gov, identifier, NCT07485348.

## Introduction

The performance in volleyball is characterized by dynamic, fast paced game with high biomechanical demands, frequent jumping multidirectional movements coupled with precise neuromuscular coordination (1). Both offensive and defensive phases entail intricate movement patterns, with the spike recognized as one of the most critical offensive skills. During a spike, athletes strive to attain optimal vertical elevation to establish a superior point of attack and enhance unpredictability. Improved vertical leap ability facilitates a more acute and powerful trajectory, maximizing scoring potential. Attacking jump is a crucial factor for enhancing performance in volleyball and the height attained during the offensive phase also contribute to the outcomes of volleyball game in both male and female athlete (2).

Anthropometric profiles are significantly related to athletic performance and are employed to examine athletes in various sports with physical growth recognized as essential for attaining outstanding athletic achievements (3). Attributes including increased height, reduced body fat percentage, and lean muscular mass substantially enhance jumping performance and agility (4). These attributes may affect joint kinematics and force production during explosive movements, improving biomechanical efficiency and mitigating the risk of overuse injuries. Comprehending the interplay between anthropometric variables, neuromuscular control, and jump-landing mechanics is essential for developing effective integrated training intervention protocol that incorporate strength, and proper landing training may improve performance and injury resilience in volleyball athletes (5).

Essential anthropometric measurements encompass stature, body mass, body mass index (BMI), limb length, and body circumference parameters, which are frequently utilized to assess body composition, adiposity, and skinfold thickness. In athletic populations, these metrics are utilized to assess body composition, monitor health status, and detect potential medical issues, including energy deficit and eating disorders (6) In addition to unchangeable characteristics like height and bone structure, the ratio of fat-free mass to fat mass significantly influences performance abilities. Athletes possessing reduced fat mass and increased lean body mass generally exhibit enhanced strength-to-mass ratios, power output, and aerobic endurance (7). Recent evidence demonstrated that agility test was significantly higher in athletes with higher muscle mass. In the context of endurance, athletes with greater lean mass presented with high level of cardiovascular fitness and recovery capacity. On the other hand, higher body fat percentage is correlated with slower sprint and agility task (8). Therefore, optimal body composition is vital to enhance movement efficiency and reaction speed during competition. Volleyball players are especially prone to musculoskeletal injuries, with the knee, ankle, and shoulder recognized as the most commonly affected areas (9). A study of the Brazilian men's national volleyball team from 2018 to 2021 recorded 28 injuries affecting 12 out of 41 players. The knee had the largest share of injuries at 11/1,000 players, succeeded by the ankle at 69/1,000 athletes (10).

These data highlight the considerable injury burden linked to the repetitive movements of jumping, landing, and spiking that characterize elite volleyball performance. Volleyball players face a significant risk of lower-limb injuries due to the repetitive nature of jumping and landing in the sport (11). During landing, it is essential to efficiently disperse the kinetic energy produced during take-off to reduce stress on the joints and soft tissues. Enhancing landing biomechanics by increasing knee flexion and regulating motion diminishes kinetic stress and improves energy absorption.

Neuromuscular and plyometric training regimens that include strength, balance, and stability exercises have demonstrated efficacy in enhancing lower-limb control and reducing injury risks among volleyball athletes (12). Neuromuscular Training (NMT) is a systematic program designed to enhance performance and mitigate injury risk by incorporating fundamental functional movement skills, that concentrate exclusively on neuromuscular control and coordination (13, 14). In contrast, integrated neuromuscular training (INMT) primarily focuses on an advanced training approach that incorporates sports specific drills and motor task to enhance athletic performance (15). Furthermore, data from systematic review and meta-analysis indicate that NMT enhances lower-limb alignment during landing task and may mitigate intrinsic risk factor for injury in volleyball athletes. These data collectively endorse that incorporating INMT protocol may improve power, injury resilience and landing mechanics in volleyball players (16).

Although numerous studies have evaluated the effectiveness of neuromuscular or plyometric training, most investigations have focused on isolated performance outcomes**,** such as vertical jump height, balance, or landing biomechanics, rather than examining multiple interrelated adaptations simultaneously (17, 18). Furthermore, much of the available evidence has been derived from basketball, soccer, and mixed-sport populations or from elite adolescent athletes, thereby limiting the generalizability of findings to adult male volleyball athletes (18, 19)**.** Previous volleyball-specific studies have primarily emphasized improvements in jump performance or injury prevention, with comparatively limited attention given to whether neuromuscular adaptations are accompanied by concurrent changes in anthropometric characteristics, body composition, and movement quality following a structured INMT program (20).

Evaluating these variables collectively is clinically and practically important because they represent complementary domains influencing volleyball performance and injury risk. Anthropometric characteristics and body composition affect force production, movement efficiency, and relative power output, whereas landing biomechanics reflect neuromuscular control and dynamic knee stability during high-impact tasks. Vertical jump height represents explosive lower-limb power, a critical determinant of volleyball performance. Since these factors interact biomechanically and physiologically, examining them within a single intervention provides a more comprehensive understanding of the adaptations induced by INMT than evaluating each outcome independently (21, 22).

In addition, INMT produces significant neuromuscular and physiological adaptations in volleyball players, such as increased flexibility, power, stability, motor competence and physical performance (23, 24). As such, this INMT incorporates various elements like motor skill development, core stability, balance and strength, all of which have a positive impact on athletic performance. Therefore, this study will aim to investigate the effects of an eight-week Integrated Neuromuscular training program on anthropometric characteristics, body composition, jump-landing biomechanics, and vertical jump height among adult male volleyball athletes. We hypothesized that structured INMT will produce significant improvements across these interrelated performance and biomechanical outcomes. The findings are expected to assist physiotherapists, strength and conditioning specialists, and volleyball coaches in designing evidence-based, sport-specific injury prevention and performance enhancement programs.

## Methodology

### Study design & ethical approval

This study will utilize a non-randomized matched controlled study approach to assess the impact of an eight-week integrated neuromuscular training (INMT) program on the anthropometric profile, jump-landing mechanics, and vertical jump height of young male volleyball athletes. Given the non-randomized matched controlled study, causal interpretation will be limited. Matching and baseline adjustment procedures will be used to reduce, but not eliminate, potential selection bias. However, certain methodological measures will be implemented to augment internal validity and to minimize bias. The participants baseline characteristics will be assessed to establish group comparability and minimize the confounding emerges from assessed variables. In addition, to reduce bias in the observation and measurement, the assessor who measured the outcome parameters will be blinded during the grouping and data collection phase (25). Participants will be divided into two groups: an Experimental Group (EG) that will receive INMT thrice a week for eight weeks, and a Control Group (CG) that maintain their standard volleyball training regimen. Despite the absence of random allocation, both groups will be comparable in baseline parameters such as age, height, weight, and body mass index (BMI). Purposive sampling will be utilized to enlist experienced volleyball players who satisfied certain inclusion criteria, guaranteeing adequate baseline proficiency and conditioning for the intervention.

This study will adopt a matched controlled allocation approach to facilitate the matching between the groups. When random allocation is not feasible, non-random grouping with a matching baseline characteristic can be employed as it is well established method to compare groups (26). Participants will be matched based on the key baseline data such as such as age, gender, training periods, training duration and frequency, playing position, competitive level to maintain the uniformity as these factors will be perceived as potential confounders that may affect the result and balancing performance. Matching will be carried out prior to group allocation by pairing participants with identical baseline characteristics to guarantee the balance between the groups. Group allocation will be based on club accessibility and training logistics rather than random selection. Subsequently, after allocation, baseline homogeneity will be assessed using ANCOVA or Friedman test for continuous variable based on distribution of data and chi-square test for categorical variables. The standardized mean difference will be computed to examine the extent of any remaining baseline imbalance. If significant baseline difference exists after matching the appropriate variable will be included as covariates in the primary analyses to minimize the residual confounding. To mitigate expectation effects, the outcome assessor will be blinded to the group allocation, and the statistical analyses will be employed using data coding procedure to explicit the exposure of group allocation.

The study will be conducted at private volleyball clubs located in Nilai and Subang, Malaysia. Ethical approval has been obtained from the University Research and Ethics Panel with ref. no. INTI-IU/FHLS-RC/BPHTI/1NY12025/007 and adhered to the declaration of Helsinki. This non-randomized matched controlled study has been registered with ClinicalTrials.gov (NCT07485348). The exercise intervention will be delivered by a sports physiotherapist who had over 10 years of experience in the relevant field. All participants will be briefed about the study's objectives and procedures. The participation of the subjects in this study will be voluntary, and each participant would be expected to sign the informed consent form before participation. Subjects will be allowed to discontinue from the study if they experience any form of musculoskeletal injury or any adverse effects observed during the delivery of the intervention. Any form of harm during the session will be documented through observation and self-reporting measures.

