## Intervention protocol

The intervention for both groups will have a matched warm up and cool down phase of 10 min and 5 min respectively along with 45 min of structured exercise protocol, a 1-minute rest interval will be provided between each set for both groups. The intervention regimen for the experimental group comprised an 8-week structured neuromuscular training program conducted thrice a week, in conjunction with regular volleyball practice. Each 60-minute session will commence with a 10-minute dynamic warm-up that incorporated mobility and stretching exercises, including lunges with trunk rotation, leg swings, and jogging. Borg scale of rate of perceived exertion (RPE) will be used to prescribe the exercise intensity for both groups. The exertion level will be maintained between 13 and 16 (somewhat hard to hard). RPE will be recorded after each training session and utilized to guide progression when appropriate. Training load during each session will be closely monitored through RPE method (session × perceived exertion score). The primary training phase will include 45 min of incremental neuromuscular activities aimed at improving proprioception, balance, and lower-limb control. In the initial four weeks (Foundation phase), participants will be instructed to execute bodyweight squats, bilateral stance on BOSU ball, unilateral stance with contralateral leg swing, Jump and freeze, Lateral bounds, Single Leg Romanian Deadlift. Progression of the training load will be implemented every 4 weeks by modifying exercise complexity, balance challenge, repetitions and external resistances. Each progression will be allowed only when participants performed correct technique without any compensatory movement patterns during two consecutive sessions. The training intensity and complexity will be incrementally elevated from weeks five to eight (Advanced neuromotor phase) through the incorporation of barrier Jump front cone runs, Single leg hops (lateral + forward) and Zig-zag cone drills, Single Leg Romanian Deadlift. A one-minute rest interval will be provided between sets, and each session will be concluded with a 5-minute cool-down comprising light jogging and static stretching [EG training Protocol is specified in Table 1]. In contrast, the CG will continue their routine volleyball training supplemented with a structured resistance-training program over the same period. Approximately 60 min per session [CG training Protocol is specified in Table 2]. This design will ensure that any observed differences between groups could be attributed to the neuromuscular component rather than general training volume or duration. The training protocol for EG will be adopted and modified from the previous studies (31–33). The training regimen for CG will be derived from validated earlier protocols in volleyball specific conditioning studies (34, 35). Participants will be instructed not to engage in any other structured interventions that are designed to improve body composition and movement patterns during the intervention session. To maintain the fidelity, all the sessions will adhere to a standard training manual, consistent exercise sequence, progression timeline. All training sessions will be conducted at the indoor volleyball training facility centre equipped with a suitable training surface, and the intervention will be closely supervised by the qualified sports physiotherapist to ensure proper exercise execution, deliver feedback and minimize injury risk. A 85% regular attendance rate will be mandatory to comply with the intervention protocol. Adverse events such as musculoskeletal strain, sprains or any other form of sports related incidents will be recorded and reported to ethical committee by the principal investigator throughout the study. In addition, upon completion of the intervention protocol, all outcome parameters will be measured immediately on the same day using a randomized test sequence for all groups, with the same investigator being assigned to collect data to avoid bias of the assessor between the pre- and post-intervention period in the same environment.

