**Neuromotor Foundation Phase — Weeks 1–4 (Low-to-moderate intensity)**									
1–4	Session 1: Balance & Plyometrics	Bilateral stance on BOSU ball; unilateral stance with contralateral leg swing (40° flexion–extension); heel raise and balance on one knee on BOSU ball; balancing while catching a tennis ball	3	30 s/leg	1 min between sets	Low–moderate	Progress to Weeks 5–8 protocol once balance is maintained without loss of postural control or compensation	Direct supervision by physiotherapist	Non-slip mat under BOSU ball; physiotherapist spots throughout to prevent falls
		Jump and freeze	3	10 reps	1 min between sets	Low–moderate	Increase landing control demand before advancing to Weeks 5–8		Land softly with knees soft; therapist checks landing mechanics
		Lateral bounds	3	10 reps	1 min between sets	Low–moderate	Increase distance/speed before advancing to Weeks 5–8		Clear surrounding area; supportive footwear required
		Squat jump	3	10 reps	1 min between sets	Low–moderate	Progress jump height/complexity before advancing to Weeks 5–8		Cue soft landing; therapist monitors knee alignment
		Ankle hops	3	10 reps	1 min between sets	Low–moderate	Progress repetitions/speed before advancing to Weeks 5–8		Perform on non-slip surface; stop if ankle discomfort occurs
	Session 2: Agility & Strength Training	T-drill	3	4 reps	1 min between sets	Low–moderate	Advance to Weeks 5–8 multidirectional drills once technique is consistent		Clear drill area of obstacles; appropriate footwear
		4-corner sprint drill	3	4 reps	1 min between sets	Low–moderate	Advance to Weeks 5–8 multidirectional drills once technique is consistent		Ensure adequate spacing between participants
		Ladder feet drill	3	4 reps	1 min between sets	Low–moderate	Advance tempo before progressing to Weeks 5–8		Check ladder is secured flat on floor
		Lunges (front & back)	3	10 reps	1 min between sets	Low–moderate	Progress load/range before advancing to Weeks 5–8		Monitor knee tracking over toes
		Bilateral calf raises on step	3	10 reps	1 min between sets	Low–moderate	Progress to Weeks 5–8 loading		Hold support rail if balance is unsteady
		Single-leg Romanian deadlift	3	10 reps/leg	1 min between sets	Low–moderate	Progress to Weeks 5–8 loading once form is consistent		Maintain neutral spine; therapist corrects hip hinge pattern

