**Strength Training Phase 1 — Weeks 1–4 (Moderate intensity)**									
1–4	Resistance Training	Barbell hip thrust	3	10 reps	1 min between sets	Moderate	Load progressed to Weeks 5–8 exercise variation once technique is consistent	Direct supervision by physiotherapist	Spotter present; verify bar/pad positioning before loading
		Leg press	3	10 reps	1 min between sets	Moderate	Load progressed to Weeks 5–8 exercise variation once technique is consistent		Confirm seat/carriage setting; avoid locking knees at end range
		Romanian deadlift	3	8 reps	1 min between sets	Moderate	Progressed to single-leg variation in Weeks 5–8		Maintain neutral spine; therapist corrects hip hinge pattern
		Barbell back squat	3	8 reps	1 min between sets	Moderate	Progressed to front squat/half-squat variations in Weeks 5–8		Spotter present; monitor knee tracking and lumbar position
		Standing bilateral heel raise	3	10 reps	1 min between sets	Moderate	Load progressed in Weeks 5–8		Hold support rail if balance is unsteady

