**Strength Training Phase 2 — Weeks 5–8 (Moderate-to-high intensity)**									
5–8	Resistance Training	Walking dumbbell lunges	3	12 reps/leg	1 min between sets	Moderate–high	Increased load/volume relative to Weeks 1–4 lunge pattern	Direct supervision by physiotherapist	Ensure clear walking path; monitor knee tracking
		Deadlift	4	8 reps	1 min between sets	Moderate–high	Increased sets and load relative to Weeks 1–4 Romanian deadlift		Spotter present; maintain neutral spine throughout lift
		Single-leg glute bridging	3	12 reps/leg	1 min between sets	Moderate–high	New unilateral variation introduced in this phase		Maintain pelvic alignment; stop if lumbar discomfort occurs
		Front squat	3	12 reps	1 min between sets	Moderate–high	New squat variation introduced in this phase		Spotter present; monitor bar rack position and torso angle
		Barbell half squat	3	12 reps	1 min between sets	Moderate–high	New squat variation introduced in this phase		Spotter present; control depth to avoid excessive load on knees
		Single-leg Romanian deadlift	3	12 reps	1 min between sets	Moderate–high	Progressed from bilateral Romanian deadlift in Weeks 1–4		Maintain neutral spine; therapist corrects hip hinge pattern

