## Conclusion

This protocol will provide preliminary evidence whether incorporation of an 8-week integrated neuromuscular training program can improve landing mechanics, vertical jump performance, anthropometric and body composition-related outcomes in male volleyball athletes in addition to regular training program.

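### The control arm is described as usual volleyball training in one place and volleyball plus resistance training elsewhere, and the attribution and conclusion sentences are not worded to either contrast

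*Protocol article*

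**What the plan says.** The control arm is described in four places in the protocol article.

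- Study design & ethical approval: an experimental group receiving INMT three times a week is set against "a Control Group (CG) that maintain their standard volleyball training regimen". No added programme is mentioned.
- Abstract, Methods: "control group (volleyball training along with a structured resistance training program".
- Intervention protocol: "the CG will continue their routine volleyball training supplemented with a structured resistance-training program over the same period", at about 60 minutes per session.
- Table 2: a physiotherapist-supervised programme, three sessions a week for 8 weeks, with five resistance exercises in weeks 1–4 and six in weeks 5–8.

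The Intervention protocol section then says of the comparison: "This design will ensure that any observed differences between groups could be attributed to the neuromuscular component rather than general training volume or duration". The Conclusion expects preliminary evidence on whether INMT can improve outcomes "in male volleyball athletes in addition to regular training program". The aim and hypothesis at the end of the Introduction name no comparator. The primary analysis (Data analysis) is a group × time interaction test.

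**The concern.** A group × time test takes its meaning from what the control group does. With controls on usual volleyball training, it asks what INMT adds. With controls on volleyball plus resistance training, it asks whether INMT does better than a different active programme.

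The two readings give different conclusions from the same data. Against an active comparator, a null interaction could arise because both programmes work. Body composition is a primary outcome that resistance training may itself change, so a difference there could favour the controls. A reader of the Conclusion, which does not mention the resistance programme, could take either result as an answer to the add-on question.

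The attribution sentence raises the stakes because it promises in advance that any difference can be credited to one component.

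**Working it through.** **1. Can the Study design sentence be shorthand for the fuller description?** It says controls keep a standard regimen. The Intervention protocol section says the routine regimen is supplemented, so the resistance work is additional to it. Sample size and participants also excludes players taking part in other structured training programmes, so such a programme is not part of what participants already do. The two descriptions therefore define different comparators.

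**2. Does the attribution sentence hold under either description?**

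- *Volleyball plus resistance (Table 2).* Session time is matched: 10 + 45 + 5 = 60 minutes in both arms. The rest interval (1 minute) and the target RPE (13–16) are also the same. But the arms differ in two ways at once. The experimental arm gets balance, plyometric and agility work with lighter strength work. The control arm gets a barbell and machine programme that the experimental arm does not. The contrast is between whole programmes and does not isolate one component.
- *Volleyball only.* The experimental arm would have 3 × 60 = 180 minutes a week of supervised training that controls lack, so volume and duration could not be ruled out.
- *Either way.* The Study design section says causal interpretation will be limited and that allocation is by club accessibility and logistics. A design with those features cannot ensure attribution.

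**3. Do the tables show matched volume?** Inputs are the sets columns of Tables 1 and 2. Two assumptions are needed. Table 1 lists two session types for three weekly sessions, so a 2:1 split in either direction is assumed. The balance row lists several exercises against a single entry of 3 sets, so both readings are shown.

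Sets per session, experimental arm:

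- Weeks 1–4, Session 1: 4 balance exercises × 3 + 4 × 3 = 24, or 3 + 12 = 15 if the row is 3 sets in total. Session 2: 6 × 3 = 18.
- Weeks 5–8, Session 1: 3 balance exercises × 3 + 5 × 3 = 24, or 3 + 15 = 18. Session 2: 3 × 2 + 2 × 3 = 12.

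Sets per session, control arm: 5 × 3 = 15, then 3 + 4 + 3 + 3 + 3 + 3 = 19.

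| Sets per week | INMT, 3 sets per balance exercise | INMT, 3 sets for the balance row | Control |
|---|---|---|---|
| Weeks 1–4 | 24 + 2×18 = 60 to 2×24 + 18 = 66 | 2×15 + 18 = 48 to 15 + 2×18 = 51 | 3×15 = 45 |
| Weeks 5–8 | 24 + 2×12 = 48 to 2×24 + 12 = 60 | 18 + 2×12 = 42 to 2×18 + 12 = 48 | 3×19 = 57 |

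In weeks 1–4 the experimental arm has more sets on every reading. In weeks 5–8 it has fewer on the second reading, and its range spans the control figure on the first. No reading gives equality in both phases.

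**4. Intensity (secondary).** In weeks 1–4 Table 1 is labelled low-to-moderate and Table 2 moderate, while the Intervention protocol section prescribes RPE 13–16, glossed as somewhat hard to hard, for both groups. In weeks 5–8 both tables are labelled moderate-to-high. No mapping between the labels and the RPE range is given.

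**The case against.** The strongest reply is that one summary sentence is out of line and nothing more. It is brief for both arms: it also leaves out the experimental group's volleyball training. The abstract, the intervention text and a full exercise table agree with each other, and nobody following Table 2 could deliver a volleyball-only control arm. The Conclusion's phrase correctly describes what the experimental group receives. Session time, rest and target exertion are matched.

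Much of this stands. The sentence does not say that controls do volleyball training only, and the duration half of the attribution sentence is supported. But the sentence is the formal statement of the design, and it omits a complete supervised programme. As a statement of what the trial will show, the Conclusion does not fit a comparison with resistance training.

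A reader might also infer more than the document supports:

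- *That the aim and hypothesis pose an add-on question.* They name no comparator at all.
- *That the experimental arm simply trains a third to a half more.* That holds only for weeks 1–4 under one reading of the balance row. Under the other reading the excess is 3 to 6 sets on 45, and the direction reverses in weeks 5–8. Sets are also a crude measure across timed holds, sprint drills and loaded lifts.
- *That the single-leg Romanian deadlift in both arms defeats attribution.* A shared component tends to cancel in the contrast, and controls have it only in weeks 5–8.
- *That intensity differs throughout.* The labels differ only in weeks 1–4. They are given per exercise, whereas RPE is recorded per session.
- *That within-group change will be used as evidence of effect.* The planned primary test is between groups.

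**Conclusion.** The point holds. The comparator of the primary test is stated inconsistently, and this must be settled before the result can be interpreted. This review does not say which control regimen is right.

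The attribution guarantee is unsupported under either description. That conclusion rests on the difference in programme content, the non-random allocation and the article's own caveat on causal interpretation. It does not depend on the set counts. Those show only that matched volume is not demonstrated, and they rest on the assumed 2:1 session split and on how the balance row is read. The mismatch between the intensity labels and the RPE range is a lesser matter.

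**What to change.** 1. Reconcile the Study design section with the abstract, the Intervention protocol section and Table 2, so that one control arm is described throughout. Check that the registry entry, which is not shown here, agrees.
2. Name that comparator in the aim and hypothesis, and word the Conclusion to the same contrast. If Table 2 stands, the contrast is INMT against resistance training, each added to volleyball, and the text should say that a null result would mean no detected advantage over resistance training.
3. Replace the attribution sentence. If Table 2 stands, it could say that session time, rest interval and target exertion are planned to be equal, and that any remaining difference reflects the two programmes as wholes together with possible differences between clubs.
4. Report the session-RPE training load, which is already to be monitored, by arm. State how the third weekly session is assigned and how many sets the balance row represents.
5. Reconcile the weeks 1–4 intensity labels with the RPE range stated for both groups.

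The cost is wording and one descriptive summary of data already planned, with no added measurements. If Table 2 stands, the price is a narrower claim.
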